### **6.3. Data management**

#### **6.3.1. Source Data**

The source documents are all information collected from subjects. This includes paper CRFs, electronic CRFs and electronic spreadsheets. All paper documents will be stored safely in confidential conditions, such as lockable safe/filing cabinets.

Most subject data is collected using REDCap. REDCap is a web application for building and managing online databases. Data stored within REDCap, information pertaining to the identity and activities of REDCap users are well protected. REDCap is installed under the IT infrastructure and environment in PolyU. Both the web server and database server are located behind the firewall of PolyU. Multi-factor authentication is required for the users to gain access to REDCap. Users will need to connect to a dedicated virtual private network using Microsoft multi-factor authentication pre-registered and installed in their smartphone, and then enter use a different set of login and password to login REDCap. Each user has their own account for the REDCap access to the project. Limited access to various functionality and modules such as being able to export data, to enter data or to modify the user privileges could be set up according to the role of investigators. Data Access Group could be implemented to segregate users in PolyU so the users will only gain access to necessary items to protect the privacy of the subject.

Access to the REDCap will be limited to study staff only. Anonymized patient identifiers will be used on all trial-specific documents, other than the signed consent forms and electronic folder of the participant (only available to the unmasked Investigators). The subjects will be referred to by unique registration numbers, not by name.

### 6.3.2. Data recording and record keeping

Direct access will be granted to authorized study staff from PolyU. All examination data will be collected by research optometrists and administrative personnel and recorded directly onto the CRFs in REDCap. If examination printouts are required to be uploaded to REDCap, researchers need to remove the subject's name and identifying information, and only write down the subject's unique study ID.

Each CRF should be completed within 3 working days of the subject visit. Data verification is conducted by unmasked researchers within 7 working days of CRFs completion.

Data will be backed-up onto a secure central cloud server. Only authorized, trained personnel will have access to the electronic data. The subjects will be identified by a unique registration number and/or code in the spreadsheet. The name and any other identifying detail will not be included in any electronic files.

Standard procedures for data management are prescribed in the Manual of Procedures.

## **7. Ethical approval and Consent**

### **7.1. Human ethics approval**

Study protocol, participant information sheet and consent form have received approval from the Human Subjects Ethics Sub-committee (HSESC) of the Institutional Review Board (IRB) of PolyU (HSEARS20221223001).

### **7.2. Informed consent/assent**

Prior to or at the very beginning of the baseline visit, subjects and parents/guardians shall be fully informed of the details of research study participation.

Informed consent must be obtained from parents/guardians. Researchers shall ensure that the parents/guardians fully understand the purpose of the research study, the potential risks and benefits, the study procedures and duration, and any alternative options available.

Informed assent is obtained from subjects (child) as it is used specifically for persons who are not able to give legal consent to participate in the study. The age range for informed assent ranges from 7 to 18 years old typically. If the child is under 7 years old and lacks cognitive ability to provide informed assent, the parents/guardians will

be asked to provide informed consent on their behalf. While the child may not be able to provide informed assent, researchers shall make effort to explain the research study in age-appropriate language and help the child understand the information. It is important to involve the child in the decision-making process and to ensure they feel comfortable and safe throughout the study.

The consent/assent forms must be signed and dated by the parents/guardians and/or subjects as required and by the researchers obtaining the consents/assents. One copy of the signed consent/assent form will be given to parents/guardians.

A contact number will be provided to parents/guardians if they wish to inquire or obtain more information about the research study. The responsible research staff are [name] or [name] at Tel/WhatsApp: xxxx xxxx during business hours (9:30 A.M. to 5:45 P.M., Monday through Saturday, except on public holidays).

Standard procedures for obtaining consents/assents are described in the Manual of Procedures.

## **8. Assessment of Safety/Adverse Event Reporting**

### **8.1. Definitions**

#### **8.1.1. Adverse event (AE)**

An Adverse event (AE) is any untoward medical occurrence, unintended disease or injury, or untoward clinical signs (including abnormal laboratory findings) in a clinical investigation subject administered a pharmaceutical product and which does not necessarily have to have a causal relationship with the treatment.

AEs can be:

1. A new disease or symptom that was not present at baseline (enrolment)
2. An increase in the severity or frequency of a pre-existing symptom or condition
3. Abnormal laboratory test results

#### **8.1.2. Serious Adverse Event (SAE)**

A serious adverse event (SAE) is an adverse event that leads to any of the following:

1. Results in death
2. Is life-threatening, or places the participant at immediate risk of death from the event as it occurred
3. Requires hospitalization or prolongs an existing hospitalization,
4. Causes persistent or significant disability or incapacity
5. Results in congenital anomalies or birth defects
6. Is another condition that investigators judge to represent significant hazards
7. Planned hospitalization for a pre-existing condition, or a procedure required by the investigational plan, without serious deterioration in health, is not considered a serious adverse event.

#### 8.1.3. Adverse device effect (ADE)

An Adverse Device Effect (ADE) is an adverse event related to the use of an investigational medical device.

1. This definition includes adverse events resulting from insufficient or inadequate instructions for use, deployment, implantation, installation, or operation, or any malfunction of the investigational medical device.
2. This definition includes any event that is a result of an user error or intentional abnormal use of the investigational medical device.
3. The definition includes the ‘comparator’ if the comparator is a medical device.

#### 8.1.4. Serious adverse device effect (SADE)

A Serious Adverse Device Effect (SADE) is an Adverse Device Effect that has resulted in any of the consequences characteristic of a Serious Adverse Event.

#### 8.1.5. Unanticipated problem (UP)

It is an adverse event or adverse device effect was not previously identified in nature, severity, or degree of incidence in the investigational plan, Investigator's brochure or protocol.

#### 8.1.6. Device deficiency

Device deficiency is any inadequacy of a medical device concerning its identity, quality, durability, reliability, safety or performance:

1. Includes malfunctions, use errors, and inadequacy in the information supplied by the manufacturer including labelling.
2. Includes device deficiencies related to the investigational medical device or the comparator.

Adverse Events (AEs), Serious Adverse Events (SAEs), Adverse device effects (ADEs), Serious adverse device effects (SADEs), unanticipated problem (UP) and device deficiency for the research study will be recorded through REDCap.

### 8.2. Classification of an adverse event and adverse device effect

#### 8.2.1. Causality

Worsening of visual acuity, development of visual disturbances (such as diplopia, ghosting, glare), eye strain symptoms, symptoms of eye infection or allergic responses (such as redness, pain, decreased vision, discharge, increased light sensitivity) are to be noted onto REDCap. An adverse event may or may not be causally related to the study intervention. The relationship of each adverse event to the trial treatment must be determined by a clinically qualified individual according to the following definitions:

- **Related:** The adverse event follows a reasonable temporal sequence from trial treatment. It cannot reasonably be attributed to any other cause.
- **Not Related:** The adverse event is probably produced by the participant's clinical state, by other modes of therapy administered to the participant or is otherwise unrelated to the trial treatment.

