### 8.4. Reporting

**Related Serious adverse events must be reported to the IRB and the sponsor of the study by the Investigator as soon as possible**, the IRB of the Hong Kong Polytechnic University requires related SAE be reported within 48 hours. ICH and the U.S. Food and Drug Administration require fatal SAE be reported within 7

calendar days while non-fatal SAE be reported within 15 calendar days. If a serious related and unexpected AE represents an increased risk to the subject, or affects willingness to continue in the study, that information will be provided to the subject(s) and parent/guardian(s) through an update to the consent/assent, approved by the IRB, as soon as possible.

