### **8.6. Unmasking**

This is a double-masked trial, where both subjects and Investigators are masked to treatment allocation. Unmasking will only occur at the end of the study under the authorization of the project co-ordinator.

For individual emergency unmasking, where a related serious adverse event has occurred and the group allocation of the subject is required in order to enable clinical treatments to be planned, project co-ordinator will inform the allocation of the subject, and this will be documented. The masked Investigator will remain masked.

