**12.6. Reporting schedule**

The project coordinator will provide annual reports of study progress to the IRB of PolyU and the sponsor of the study. All related SAEs that are fatal or life-threatening and suspected of being related to the treatment used in the trial will also be reported within 48 hours.

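### The two causality categories in 8.2.1 do not cover every event: a possibly lens-related serious event fits neither, so it can escape reporting rules that depend on 'related'

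*Protocol*

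**What the plan says.** Classification is compulsory and has two outcomes. Section 8.2.1 states: "The relationship of each adverse event to the trial treatment must be determined by a clinically qualified individual according to the following definitions". 'Related' has two parts: "The adverse event follows a reasonable temporal sequence from trial treatment", and then "It cannot reasonably be attributed to any other cause". 'Not Related' reads: "The adverse event is probably produced by the participant's clinical state, by other modes of therapy administered to the participant or is otherwise unrelated". There is no possible or unknown category and no rule for doubtful cases.

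Several rules then use the word:

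- Section 8.4: "Related Serious adverse events must be reported to the IRB and the sponsor of the study by the Investigator as soon as possible", and "the IRB of the Hong Kong Polytechnic University requires related SAE be reported within 48 hours". The same section provides for a consent update after a serious event that is both related and unexpected.
- Section 8.6 permits individual emergency unmasking "where a related serious adverse event has occurred and the group allocation of the subject is required" to plan treatment.
- Sections 8.1.3 and 8.1.4 define an adverse device effect (ADE), and its serious form (SADE), by relation to use of the device.
- Section 12.6, with a limit of 48 hours: "All related SAEs that are fatal or life-threatening and suspected of being related to the treatment used in the trial will also be reported within" that limit.
- Section 6.2 ties stopping of treatment to a treatment-related adverse event.

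Section 8.3 asks for relatedness to the study procedures as well as to the device, whereas 8.2.1 defines it for the trial treatment only.

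**The concern.** A two-way classification that every event must pass through has to be exhaustive, and the doubtful cases should have a stated destination. Here 'Related' is set at the level where no other cause is reasonable, and 'Not Related' at the level where another cause is probable. The ground between them is where a possibly device-related event lies.

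Such events can be expected in this trial. Section 5.4 lists blur, dizziness and disturbed binocular vision as possible effects of the spectacles, and blurred near vision and light sensitivity as possible effects of the eye drops. Some of these symptoms can have another reasonable explanation in a child. Most will not be serious, but the definition that governs them also governs the serious ones. An example would be a fall with hospital admission soon after new lenses are dispensed, where inattention is a reasonable but not a probable explanation.

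At stake is whether the IRB and the sponsor hear promptly of a serious event that the lens may have caused. Section 8.7 sets up no independent safety committee, and the monitor's duties described there are consent and data checks, not review of causality.

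**Working it through.** No arithmetic applies and the plan states no figure on this point. The check has two steps: whether the definitions cover every case, and what depends on them.

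**Step 1: coverage.** Take an event that follows treatment in a plausible time sequence.

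| Other cause | Meets 'Related'? | Meets 'Not Related'? | Class |
|---|---|---|---|
| None that is reasonable | Yes | No | Related |
| Probable | No | Yes | Not Related |
| Reasonable, but not probable | No, it can reasonably be put down to something else | No, the other cause is not probable | None |

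The closing words of 'Not Related' (unrelated in some other way) do not catch the third row. They apply to an event already judged unrelated, and in the third row that judgement cannot be made.

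**Step 2: what depends on the class.** Sections 8.1.3, 8.1.4, 8.4, 8.6 and 12.6 give no other definition of 'related', so I read them with 8.2.1.

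| Rule | Is 'related' a condition? | Third-row SAE |
|---|---|---|
| Report to IRB and sponsor, 48 hours for the IRB (8.4) | Yes | Not triggered |
| Consent update (8.4) | Yes, together with serious and unexpected | Not triggered |
| Emergency unmasking (8.6) | Yes, and allocation must be needed to plan treatment | Not triggered |
| ADE/SADE status (8.1.3, 8.1.4) | Yes | Undetermined |
| Recording in REDCap (8.2.2, 8.5) | No | Recorded |
| Primary safety outcome (Section 1) | No, all adverse events | Counted |
| SAE summary (6.2) | No, all SAEs | Counted |

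**Step 3: related wording that does not match.**

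- Section 8.4 applies 48 hours to related SAEs in general. Section 12.6 names the fatal or life-threatening ones and requires both 'related' and 'suspected of being related'. The second term is looser than 8.2.1, so two thresholds are stacked.
- Section 8.4 also cites 7-day and 15-day limits for SAEs without the word 'related'.
- Section 6.2 stops treatment for any treatment-related event, while 8.5 leaves it to the research team's judgement whether an event requires discontinuing the participant.
- Section 5.9 says scheduled visits and data collection end once treatment is discontinued. Section 8.5 requires follow-up visits for trial assessment after a discontinuation or withdrawal because of an adverse event.

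The last two items matter because any change to the meaning of 'related' passes through them.

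**The case against.** The strongest reply is that little in the trial's results depends on this. All adverse events are recorded whatever their cause, the primary safety outcome has no relatedness filter, and 6.2 summarises every SAE. The randomised safety comparison is therefore untouched. That stands.

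A clinically qualified assessor may also use the latitude in the word 'reasonably' and class a doubtful event as 'Related'. That may happen, but the text does not direct it and the wording points the other way.

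Four stronger readings are tempting and are not supported:

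- **Biased safety conclusion.** A reader might infer that ADE/SADE counts are pushed toward zero and that the safety conclusion fails with them. No section makes those counts an outcome, and 8.1.3 expressly includes user error and inadequate instructions.
- **A size for the shortfall.** If a fraction f of lens-caused events had another reasonable explanation, at most 1 - f would be counted; an assumed f of 50% to 90% gives 50% to 10%. This only restates the assumption. The protocol has no basis for f, and doubtful events have no assigned class, so they need not all be filed as 'Not Related'.
- **A flat contradiction on the 48 hours.** Section 12.6 names a subset of the events in 8.4 and does not exempt the rest. The scope and the term differ and should be aligned, but following 8.4 also meets 12.6 for the IRB.
- **Blocked unmasking.** Section 8.6 also requires that allocation be needed for treatment, and under 5.6.1 unmasked investigators dispense the lenses. The practical effect is probably small.

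One further objection changes the remedy. Because of 6.2 and 5.9, a wider 'Related' could by itself lead to more discontinuations and lost 12-month data. That also stands, and the fix has to deal with it.

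**Conclusion.** The gap is real. As written, 8.2.1 gives no class to an event with plausible timing and a reasonable but not probable alternative cause. A serious event of that kind does not meet the condition for reporting to the IRB and sponsor, for a consent update or for emergency unmasking, and its SADE status is left open. The consequence is confined to these safety processes. Data capture, the primary safety outcome, the SAE summary and the efficacy analysis do not depend on it.

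The size cannot be estimated from the protocol; serious events possibly due to a spectacle lens are likely to be few. The conclusion assumes that 'related' carries the 8.2.1 meaning wherever it appears, and that assessors apply the definitions as written. It is worth correcting because the matter is participant safety and the change is mainly one of wording.

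**What to change.** 1. In 8.2.1, define 'Related', for causality classification and safety reporting, as a reasonable possibility that the trial treatment or a study procedure caused or contributed to the event. Including procedures brings 8.2.1 into line with 8.3.
2. State that any event not clearly meeting 'Not Related' is handled as 'Related' for reporting.
3. Give 8.4 and 12.6 the same 48-hour scope and one term, either 'related' or 'suspected of being related'.
4. Reconcile 6.2 with 8.5 on stopping treatment, and 5.9 with 8.5 on follow-up afterwards, so that the wider reporting definition does not alter treatment stopping by accident. Which clinical rule applies is for the sponsor and the investigators to decide.

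The cost is a wording amendment and matching help text on the adverse event form, with no new data and no change to the efficacy analysis. A few more events will be classed as related and reported. That downside stays small only if item 4 is settled together with items 1 and 2.

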### 8.2.2. Severity

All AEs and other incidents occurring during the trial that are observed by study personnel or reported by the participant will be recorded onto REDCap, whether attributed to trial treatment. The following information will be recorded: description, date of onset and end date, severity, assessment of relatedness to trial intervention, other suspect drug or device and action taken. Follow-up information should be provided as necessary. The severity of events will be assessed on the following scale:

- **Mild:** Events require minimal or no treatment and do not interfere with the participant's daily activities.
- **Moderate:** Events result in a low level of inconvenience or concern with the therapeutic measures. Moderate events may cause some interference with functioning.
- **Severe:** Events interrupt a participant's usual daily activity and may require systemic drug therapy or other treatment. Severe events are usually potentially life-threatening or incapacitating. Of note, the term "severe" does not necessarily equate to "serious"

### 8.3. Responsibility

In accordance the guideline for good clinical practice (GCP) by the International Council for Harmonization of Technical Requirements for Pharmaceuticals for Human Use (ICH), the Investigator/institution should ensure that adequate medical care is provided to a subject for any adverse events, including clinically significant laboratory values, related to the trial. The Investigator/institution should inform a subject when medical care is needed for an intercurrent illness of which the Investigator becomes aware. The unmarked Investigator and the PI need to evaluate the AE severity as well as the relatedness to the study procedures and study device.

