### *Primary safety outcome*

- Adverse events, including biomicroscopic findings, for the treatment and control groups over 2 years

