## **5.6. Study intervention**

### **5.6.1. Phase 1: Two-arm RCT**

This study is a double-masked RCT. Subjects and parents are masked from the type of investigational lenses they are wearing. Masked Investigators will be responsible for masked measurements of the primary and secondary efficacy outcomes at the baseline and 6-monthly visits. Masked Investigators will never examine the subjects while they are wearing their spectacle lenses. Unmasked Investigators will conduct the remaining measurements and dispense the investigational lenses.

Eligible subjects will be randomly assigned to the control or the treatment group in an equal ratio. The control group will receive placebo SV lenses, while the treatment group will receive D2 lenses.

Scheduled visits will be conducted over a period of 2 years. The control group will cross over to wear D2 lenses at 12 months and all subjects will continue wearing D2 lenses for an additional 12 months.

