### **5.8. Masking**

The study will be double-masked. The primary and secondary outcome assessments will be performed by masked Investigators and the subject and parents/guardians will be masked to group allocation and study intervention until the data analysis is completed.

Masked Investigators will perform masked measurements of the primary and secondary efficacy outcomes (cycloplegic auto-refraction and axial length) at every 6-month visit. The masked Investigators will not be allowed to enter subjects' eye examination room and check their glasses, other than to perform their masked examination duties. Subjects will be told not to discuss their lens wear with the masked Investigator.

The children will be asked to wear the spectacles full-time. Compliance will be regularly monitored at every follow-up visit and through the completion of a questionnaire regarding their lens use.

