### 6.2. Statistical analysis

Data from the right eyes will be used for analyses when both eyes show fast progression. If only one eye demonstrated fast progression, that specific eye would be used for analyses. Demographic and optometric data will be displayed as mean and standard deviation, or number and percentage as appropriate. The Chi-square test (or if appropriate, Fisher's Exact test) and unpaired t-test will be performed to compare baseline between-group differences in demographics (age, sex). Myopia progression will be calculated as the difference between SER and AL at the baseline, the 6-month and the 1-year visits, respectively.

The unpaired t-test will be used to compare the changes in primary and secondary outcomes between groups. The efficacy of myopia control of DIMS lens will be determined by dividing the difference in myopia progression (or axial elongation) between two groups with the myopia progression (or axial elongation) in the SV group, then multiplied by 100%. Multiple regression analysis will be employed to identify factors that may be associated with myopia control efficacy. Regarding visual performance and comfort, subjective ratings collected by questionnaires will be compared between groups using Mann-Whitney U test.

Treatment will be discontinued if any treatment-related adverse event arises, such as constant visual disturbance (e.g., ghosting, diplopia, glare, etc.). The number of subjects

discontinuing treatment prematurely for any reason will be summarised by reasons for discontinuation. The incidence of all serious adverse events will be summarised.

Data analysis will follow an intention-to-treat approach. Missing values of outcome variables and covariates will be replaced using multiple imputation procedures with 10 sets of imputations assuming missing at random. All analyses will be 2-tailed with a significance level of 2.5%.

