### **8.5. Documentation and follow-up**

At each study visit, the Investigator or designee will inquire about the occurrence of AEs/SAEs since the last visit. Any AE observed by the Investigator or reported by the subjects will be documented on an adverse event form onto REDCap as soon as possible after notification of the event. However, not all AEs require reporting, as they might not directly impact participant risk. Information to be collected includes event description, time of onset, clinician's assessment of severity, relationship to study product (assessed only by those with the training and authority to make a diagnosis), and time of resolution/stabilization of the event. All AEs occurring while on study must be documented appropriately regardless of relationship. All AEs will be followed to adequate resolution. An appointment will be arranged for 1-4 weeks following AE resolution to check for any recurrence or changes because of the AE. Changes in the severity of an AE will be documented to allow an assessment of the duration of the event at each level of severity to be performed. AEs characterized as intermittent require documentation of onset and duration of each episode. These will be followed-up and assessed by medically fit clinician. It will be left to the judgement of the research team to decide whether an AE is of sufficient severity to require discontinuing the participant from the study. A subject may also voluntarily withdraw from participating in the study due to what he or she perceives as an intolerable AE. If either of these occurs, the subject must undergo follow-up visits for trial assessment and be given appropriate care under medical supervision until symptoms cease, or the condition becomes stable.

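### Adverse-event severity and relatedness are rated by an Investigator who knows the lens, so graded and device-related comparisons between D2 and SV are open to rater bias of unknown direction and size

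*Protocol*

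**What the plan says.** Protocol section 8.3 names the raters: "The unmarked Investigator and the PI need to evaluate the AE severity as well as the relatedness to the study procedures and study device". Section 5.6.1 says what the unmasked staff do: "Unmasked Investigators will conduct the remaining measurements and dispense the investigational lenses". Section 5.8 limits the masked work to efficacy: "The primary and secondary outcome assessments will be performed by masked Investigators", which it specifies as cycloplegic autorefraction and axial length. Section 8.6 nevertheless says: "This is a double-masked trial, where both subjects and Investigators are masked to treatment allocation".

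The primary safety outcome in section 1 is "Adverse events, including biomicroscopic findings, for the treatment and control groups over 2 years". Section 8.2.1 lists the complaints to be noted, most of them symptoms. It requires the person judging causality to be clinically qualified, but not masked.

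On stopping, section 6.2 says: "Treatment will be discontinued if any treatment-related adverse event arises, such as constant visual disturbance". Section 8.5 says: "It will be left to the judgement of the research team to decide whether an AE is of sufficient severity to require discontinuing the participant". Section 8.7 sets up no DSMC and leaves safety monitoring to the research team.

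**The concern.** Severity and relatedness are judgements. For ghosting, glare or eye strain there is little objective sign to anchor them, and under section 8.2.1 an event counts as related only if no other cause reasonably explains it. A rater who knows whether the child wears a multi-segment or a plain lens may answer that question differently for the same complaint. The written rule is common to all arms, but it is applied with the arm known.

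At stake is any table that shows severity grades or device-related events by arm in support of the primary safety outcome. The same rating bears on who stops treatment, and so possibly on who has 12-month SER and AL data. It also bears on which serious events are reported as related under section 8.4. A reader of section 8.6 alone would believe that these ratings were masked.

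**Working it through.** The protocol gives no figure on this point, so the check sets its sections side by side.

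1. **Meaning of *unmarked*.** The protocol otherwise speaks only of masked and unmasked Investigators, and the word has no other sense in it. Unmasked is the natural reading of section 8.3.
2. **Does that rater know the arm?** Yes. Under section 5.6.1 the unmasked Investigators dispense the lenses.
3. **Does the second rater correct for this?** It cannot be said. The PI's masking status is not given, and no rule settles a disagreement between the two raters.
4. **Is there a masked safeguard elsewhere?** None is described. Masked assessment stops at autorefraction and axial length (5.6.1, 5.8), there is no masked adjudication of events, and there is no DSMC (8.7).
5. **Does section 8.6 agree?** No. Its general statement conflicts with 5.6.1 and 8.3, although its closing remark on emergency unmasking refers to the masked Investigator as one particular role.
6. **Which quantities are exposed?** Every event is recorded whatever its cause (8.2.2, 8.5), and families are masked (5.8). The count of events therefore does not pass through the relatedness rating. Severity grades and related-event counts do.
7. **For how long does the contrast exist?** Controls cross over to D2 at 12 months (5.6.1), so D2 and SV can be compared in only the first half of the 2-year safety period.
8. **Size.** The related-event rate in an arm is the event rate multiplied by the probability that an event is called related. With equal true event rates, the apparent ratio between arms equals the ratio of those two probabilities. The protocol supplies neither the rates nor the probabilities, so any ratio would only restate an assumption. The direction is also open: a rater could over-attribute complaints to D2 or excuse them.
9. **Route to the efficacy data.** A rating of treatment-related leads to stopping under section 6.2, whereas section 8.5 leaves stopping on severity to the research team. Section 5.9 says scheduled visits and data collection do not go on after treatment stops for any reason. Section 8.5 requires follow-up visits after an adverse event leads to discontinuation, at least until the condition settles. The route to missing 12-month data is open under 5.9 and at least partly closed under 8.5.

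**The case against.** The strongest reply is that the planned safety analysis hardly uses these ratings. The primary safety outcome is adverse events, not related or graded ones. Section 6.2 plans summaries of serious events and of discontinuations by reason, and states no between-arm test of relatedness or severity. This stands, and it rules out inferring that the whole harm comparison is biased.

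A reader might also infer that a plain SV lens gives the rater a written ground for scoring an event as not related. It does not: section 8.1.3 counts a comparator device within the definition of an adverse device effect, and section 5.4 attributes early blur and dizziness to the spectacles in general. Bias remains possible, but not by the protocol's own rule.

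A third inference would be that arm-aware rating will make 12-month SER and AL data unequally missing. The text does not support that while 5.9 and 8.5 conflict.

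Finally, sending symptom complaints to the masked Investigators could weaken the masking of the primary outcome, since section 5.8 tells children not to discuss lens wear with them. Event review also takes place at dispensing and one-month visits (5.16), where no masked measurement is scheduled. Both points are sound, and they shape the fix: rating from the record, not by interview.

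None of this removes the core. Section 8.3 gives the rating to someone who knows the arm, and a later analysis plan could not undo ratings made that way.

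**Conclusion.** The point holds in a limited form. Severity and device-relatedness are rated by at least one person who knows the lens, the second rater's masking is unstated, and section 8.6 says otherwise. D2-versus-SV comparisons of graded or related events, confined to the first 12 months, are open to rater bias whose direction and size cannot be determined from the protocol. Raw incidence is less exposed. An effect on the completeness of the 12-month efficacy data is possible but not established.

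The conclusion rests on reading *unmarked* as *unmasked*. A masked PI would reduce the problem but not remove it, because no rule says whose rating prevails. This is a worthwhile improvement at low cost, not a threat to the masked measurement of SER and AL.

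**What to change.** - **Section 8.3:** correct *unmarked*. Have the severity and relatedness ratings used in the safety tables made from the REDCap adverse-event record with lens type removed. The rater should be the PI, if kept masked to lens type, or an existing masked and clinically qualified Investigator who does not measure that child's SER or AL. The rater should not discuss symptoms with the child.
- **Roles:** the unmasked Investigator keeps the child's care, the recording of events and prompt reporting of serious events. State which rating applies to the safety tables, to discontinuation and to reporting.
- **Section 8.6:** say which Investigators are masked, and include the PI.
- **Sections 5.9, 6.2 and 8.5:** the sponsor should reconcile these on when treatment stops and on follow-up afterwards. No clinical rule is proposed here.

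The cost is a wording change, a view of the event form without lens type, and some extra record review. Rating from the record also covers events noted at dispensing and one-month visits. One limitation remains: a symptom description may hint at the lens.
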